## **1.4      Dose justification**

Subcutaneous administration is considered to have similar potency as the intravenous route, but has higher patient convenience and is less susceptible to plasma peak level related adverse events. As PRO051 is very stable with a long half life (as determined in monkeys), a weekly administration is sufficient to obtain continuous tissue exposure. The minimum and maximum dose levels to be applied are based on the results from the various animal studies investigating the toxicity and/or efficacy of PRO051 (please refer to the Investigator's Brochure for further details on the results from those animal studies).

## **2            Study objective(s)**

To preliminarily assess the effect of PRO051 at different dose levels in patients with Duchenne muscular dystrophy

To assess the safety and tolerability of PRO051 at different dose levels in patients with Duchenne muscular dystrophy

To determine the pharmacokinetics of PRO051 at different dose levels after subcutaneous administration in patients with Duchenne muscular dystrophy.

## 3 Study design

### 3.1 Overall study design

This study has been designed as an open label, multiple dose, escalating dose study. Depending on the MTD level, twelve to eighteen patients will be studied in four groups.

The study flow chart in Figure 3 outlines the dose escalation design of this study. Patients in the first group will receive 0.5 mg/kg, in the second group maximally 2 mg/kg, in the third group maximally 6 mg/kg and in the fourth group maximally 10 mg/kg.

[figure not shown]

Figure 3. Study flow chart with maximum dose levels to be administered.

Patients will receive one dose of PRO051 per week for 5 weeks. Each group will initially consist of 3 patients. Interim safety review for dose escalation will take place after review of all safety data that have been collected from at least up to and including the first three administrations of study medication (i.e. at least up to and including visit 4) for each patient and no prohibitive adverse events have been observed. In case of potentially dose limiting toxicity (DLT) in one of three patients in one group, this group will be expanded to six patients. In case of similar dose limiting toxicity in two or more patients, the inclusion of patients will be stopped at that dose level. Further, it will be decided if inclusion of new subjects should be stopped, or if the study should continue with a new lower dose group, or if the study should continue by expanding the previous group to six subjects. The dose level of the group which has a dose level one step below the group with similar dose limiting toxicity in two or more patients, will be considered the maximum tolerated dose (MTD).

The decision model for discontinuation or modification of dose escalation schedule is shown in Table 2.

Given the limited number of patients affected by DMD correctable by exon 51 skipping, an adaptive design was chosen to ensure that at least at the highest dose levels a reasonable number of patients could be included and that sufficient data on dose limiting toxicities could be collected. Furthermore, it was considered that the safety and tolerability profile warranting further investigations in a larger population could sufficiently be established with these group sizes.

No control group was included due to the limited number of patients available.

Patients will receive one subcutaneous treatment of PRO051 per week for a period of five weeks (i.e. five injections in total). This number of injections was considered sufficient to establish the MTD and a dose level to investigate in future studies prior to embarking on trials with longer treatment duration. After the five weeks of treatment period, the patients will continue with follow up visits till 13 weeks after the last treatment.

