| Subject sample size                                                                                      | 12-18 patients.                                                                                                                                                                                                                                                                                                                                                                                                                                                                                                                                                                                                                                                                                                                                                                                                                                                                                                                                                                                                                                                                                                                                                                                |

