**Table 2. Decision model for discontinuation or modification of dose escalation schedulea**

| Group               | DLT                                      |      | Action                                                                                                                                                                                                        |
|---------------------|------------------------------------------|------|---------------------------------------------------------------------------------------------------------------------------------------------------------------------------------------------------------------|
| If # of subjects is | And if # of subjects with similar DLT is |      |                                                                                                                                                                                                               |
| 3                   | 0                                        | Then | Continue with next higher dose group                                                                                                                                                                          |
| 3                   | 1                                        | Then | Expand group to 6 subjects                                                                                                                                                                                    |
| 3                   | 2 or more                                | Then | Determine if:
– this group should be expanded to 6 subjects
– previous group should be expanded to 6 subjects
– a new group should start with a lower dose b
– study should be stopped |
| 6                   | 1                                        | Then | Continue with next higher dose group                                                                                                                                                                          |
| 6                   | 2 or more                                | Then | Determine if:
– study should be stopped
– study should continue with next group and determine dose level for that group c                                                                    |

a. The nature of the DLT will be taken into account

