## **4      Subject selection**

### **4.1      Subject population**

Twelve to eighteen male patients aged at least 5 and not older than 16 years on the first day of drug administration with Duchenne muscular dystrophy resulting from an exon deletion correctable by treatment with PRO051.

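### The stated maximum of 18 patients does not follow from the protocol's escalation rules, which allow up to 24 in the four planned groups

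*Protocol*

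**What the plan says.** The planned size stands in four places. In the synopsis, the design row gives twelve to eighteen patients in four groups and the sample-size row gives "12-18 patients". Section 3.1 says "Depending on the MTD level, twelve to eighteen patients will be studied in four groups". Section 4.1 says "Twelve to eighteen male patients aged at least 5 and not older than 16 years".

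The rules that generate the size are in section 3.1 and Table 2. On group size, section 3.1 says "Each group will initially consist of 3 patients". On a possible DLT "in one of three patients in one group, this group will be expanded to six patients". Table 2 repeats this for one DLT in three ("Expand group to 6 subjects"). For no DLT in three, and again for one DLT in six, its action is "Continue with next higher dose group". Two or more similar DLTs lead to a choice among listed options, which include stopping and starting a group at a lower or intermediate dose. Section 3.2.1 describes successive cohorts of three to six patients.

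Section 8.5.3 says that the size was set on scientific and medical grounds, not statistical ones.

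**The concern.** A stated maximum in a dose-escalation trial should be the largest total that the escalation rule can produce, or else be marked as a cap that overrides the rule. Here it is neither. The expansion at one DLT in three and the continuation at one in six are fixed actions that apply to every group, yet 18 leaves room for only two of four groups to expand.

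The number of boys who may be exposed is a figure that ethics committees and drug supply rely on. If three or four groups each had one DLT, the stated size and Table 2 could not both be followed. No power or precision claim is affected, because none is made.

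**Working it through.** **Inputs.** Four groups (synopsis, section 3.1); three patients per group at the start (section 3.1); six after one DLT in three, and escalation after 0/3 or 1/6 (section 3.1, Table 2). The documents give no DLT rate.

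**The plan's own figures.**
- Lower limit: no DLT in any group gives 4 × 3 = 12. This reproduces.
- Upper limit: 18 arises when exactly two of four groups expand, for example 3 + 3 + 6 + 6. It also arises as 6 + 6 + 6 with a stop in the third group. Neither path is the largest.

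**What the rules allow.** A completed trial with *k* expanded groups has 12 + 3*k* patients, *k* = 0 to 4, which gives 12, 15, 18, 21 or 24. The largest, 6 + 6 + 6 + 6 = 24, needs one DLT among the first three patients of each group and none among the next three. It uses only fixed Table 2 actions. A further lower or intermediate group would add three to six patients. If escalation stops early, totals of 3, 6 or 9 are also possible.

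**How often 18 would be exceeded.** This is an illustration. Assume independent patients, the same DLT probability *p* at each dose, and inclusion ending at the first group with two or more DLTs. Define:
- *a* = P(0 of 3) = (1 − *p*)³
- *x* = P(1 of 3) = 3*p*(1 − *p*)²
- *e* = P(a group expands and escalation continues) = *x* · *a* = 3*p*(1 − *p*)⁵

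The total exceeds 18 in two ways:
- the first three groups all expand and the fourth opens, with probability *e*³;
- exactly two of the first three expand, the other has no DLT, and the fourth expands, with probability 3*e*² · *a* · *x* = 3*e*³.

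So P(N > 18) = 4*e*³. A total of 24 needs the fourth group to expand as well: P(N = 24) = *e*³ · *x*.

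For *p* = 0.10: *e* = 0.3 × 0.9⁵ = 0.1771, and 4 × 0.1771³ = 0.022.

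| Assumed *p* | *e* | P(N > 18) | P(N = 24) | P(N < 12) |
|---|---|---|---|---|
| 0.05 | 0.116 | 0.006 | 0.0002 | 0.055 |
| 0.10 | 0.177 | 0.022 | 0.0014 | 0.182 |
| 0.20 | 0.197 | 0.030 | 0.0029 | 0.488 |
| 0.30 | 0.151 | 0.014 | 0.0015 | 0.737 |

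The last column comes from enumerating every path under the same assumptions. It measures early stopping, not a conflict in the text.

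**Sensitivity.** With rates rising by dose (2%, 5%, 15%, 30%), P(N > 18) is 0.017. If, instead of stopping, one further group is added at the failed level's DLT rate (three patients, or six after one DLT), P(N > 18) rises to 0.057 at a flat 10% and 0.105 at a flat 20%. With rates of 5%, 10%, 20% and 30% by dose it is 0.198.

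**The case against.** The strongest reply is that 18 reflects an intention. Section 3.1 explains that the adaptive design was meant to secure a reasonable number of patients at the highest doses at least, and 3 + 3 + 6 + 6 = 18 fits that. Figure 3, which outlines the escalation, is not shown in the text available and may carry a limit. Both are fair. But the first is a rationale and not a rule, and neither section 3.1 nor Table 2 refers to a limit. A deliberate cap would settle the matter as well as a larger maximum would; it only has to be written down.

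The second reply is that the conflict no longer affects anyone. Section 8.3 speaks of the core part as completed and of the extension as following the dose-escalation phase. A reader might infer that the stated number would block an expansion that the safety rule requires. That could have happened during escalation, but this version gives no sign that a group could still be opened or expanded. This part of the reply stands and lowers the weight of the point.

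The third concerns the lower limit. A reader might infer that 12 is wrong too, since two or more DLTs in the first group could end inclusion at three patients. The documents do not support that. Twelve is the correct total when all four groups open. The synopsis and section 3.1 both make the size depend on the maximum tolerated dose, and both say that inclusion may stop. Early stopping below a planned number is ordinary in such a design, and here it is disclosed.

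**Conclusion.** The upper limit of 18 is inconsistent with section 3.1 and Table 2: the fixed rules allow 24 in four groups, and an added group could take the total higher. The conclusion rests on the visible text alone and needs no assumed DLT rate.

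Its practical size is small. With stopping at two or more DLTs, the chance of exceeding 18 is about 0.6% to 3% for flat assumed rates of 5% to 30%. It would be higher if the sponsor chose to add a group. The model counts any DLT, whereas Table 2 counts similar ones and lets their nature be considered, so it tends to overstate stopping.

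One could add the early-stopping probabilities and report a 20% (0.182 + 0.022) or 52% (0.488 + 0.030) chance of ending outside 12 to 18, at DLT rates of 10% and 20%. Those sums should not be used as the size of this error. Some 18 of the 20 points and 49 of the 52 are disclosed early stopping, and they depend on flat rates that the protocol does not give.

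Severity is minor.

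**What to change.** Reconcile the size with Table 2 in all four places: both synopsis rows, section 3.1 and section 4.1. Either of two wordings would do:

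- state the range that the rules allow: 12 to 24 if all four groups are completed, fewer if escalation stops early, and more only if a group is added; or
- if 18 was a deliberate cap, say so beside Table 2 and state how the cap and the expansion rule fit together.

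Which one applies is for the sponsor to say. The first changes wording only and leaves the escalation rules as they are, though any exposure or supply figure based on 18 should be checked against it. The second adds a sentence to the decision model. Since escalation is described as complete, the correction now serves mainly to make the record and the study report consistent.

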|                                                                                                                 | 
injections in total). Depending on a possible maximum tolerated dose, twelve to eighteen patients will be investigated in four groups. Each consecutive group will consist of three patients who will be treated with maximally 0.5 mg/kg, 2 mg/kg, 6 mg/kg and 10 mg/kg, respectively. Effect and safety assessments will be done at regular intervals. Prior to each dose escalation, the safety data of the first three weekly administrations of PRO051 will be reviewed. If possible dose limiting toxicity occurs in one patient of the group of three, the group will be expanded to six patients.
 
If similar dose limiting toxicity occurs in two or more patients, the inclusion of new patients will be discontinued at that dose level. Furthermore, the inclusion of new subjects into the study may be stopped, or study may continue with a lower intermediate dose level, or study may continue by expanding the cohort of the previous dose level to six subjects. The dose level of the group which has a dose level one step below the group with similar dose limiting toxicity in two or more patients, will be considered the maximum tolerated dose (MTD).
 |

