administration at 4 mg/kg/wk. It has been demonstrated for oligonucleotides that the pharmacokinetics between species extrapolates on the basis of body weight, rather than body surface area. Therefore, a species conversion factor is not required for calculating the starting dose in humans and this exception has been acknowledged in a FDA draft guidance document on estimating the maximum safe starting dose (FDA, 2005). In the previous clinical study, 0.8 mg (0.013-0.024 mg/kg) has been administered intramuscularly. The proposed dose level range for this study is 0.5-10 mg/kg/wk by subcutaneous administration. For the starting dose, this provides a safety margin of 35x compared to the NOAEL in monkeys and mice and 8x to in rats. These safety margins are considered appropriate and conservative, because (i) monkeys are considered more relevant than rodents, in particular the absolute pro-inflammatory effects in rodents have been less relevant for predicting dose limiting toxicities in humans for oligonucleotides; (ii) the subchronic monkey and mouse more closely mimic the intended clinical study in route and frequency of administration and duration of treatment; (iii) no test-item related systemic adverse event has been observed in the previous clinical study and a safety margin of >10x compared to the monkey NOAEL, the most relevant species, is considered sufficiently appropriate for a study in this population (DMD patients of 5-16 years).

Based on preliminary plasma pharmacokinetic data and non-compartmental analysis in monkeys, the maximum plasma concentration should remain below 150 µg/ml to limit acute effects. The AUC0-7d is approximately 920 µg.h/ml based on the NOAEL of 18 mg/kg/wk. In the proposed clinical study employing subcutaneous administration, the maximum dose of 10 mg/kg is expected to yield plasma peak concentration of approximately 50 µg/ml and an AUC0-7d of approximately 511 µg.h/ml.

Local reactions to subcutaneous injection (up to 250 mg) during the clinical study may occur, but these are not expected to be dose limiting. Past experience, especially with the first generation phosphorothioate oligonucleotides, indicate that fever and chills may be dose limiting toxicities. These reactions have been dose dependent, transient and well treatable.

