### **3.2.4      Method of assigning subjects to treatment groups**

This is an open study in which all study subjects will receive active treatment. Patients will be assigned to a dose level based on the sequence of entering the study.

For safety reasons, there will be an interval of at least 2 days between the start of treatment of each patient within one group.

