### **3.3.1      Treatment period**

Treatment visits take place on day 1, 8, 15, 22 and 29. Subjects will be admitted to the hospital for an overnight stay on the treatment days. Baseline assessments will be done at time point 3 to 0 hours prior to dosing. Then PRO051 is administered by a maximum of 2 subcutaneous injections (depending on the total dose to be administered) in the abdomen located at least 4 cm apart ( $t=0$  day 1, 8, 15, 22 and 29). Subjects will be monitored for approximately 30 hours (one night), during which all safety and laboratory assessments, adverse events and other assessments as indicated in the Schedule of assessments will be completed (Appendix 2: Table 5). Thereafter, the subjects can return home. On the third day after discharge (i.e.  $t=96\pm6$  hrs after dosing) patients will be contacted by telephone by the investigator to enquire about adverse events and concomitant medication.

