| MMT                             | x                      |    |                 |                 |                 |                 |                 |      | x              |      |                 |      | x     | x                       |
| Local tolerability              |                        |    | x               | x               | x               | x               | x               | x    |                |      |                 |      |       |                         |
| Adverse events                  | x                      | x  | x               | x               | x               | x               | x               | x    | x              | x    | x               | x    | x     | x                       |
| Concomitant medication          | x                      | x  | x               | x               | x               | x               | x               | x    | x              | x    | x               | x    | x     | x                       |
| Pharmacokinetic sampling        |                        |    | x  | x  | x  | x  | x  | x    | x              | x    | x               | x    | x     | x                       |

1. Visit to be performed if subject stops prematurely (for any reason)
2. All screening assessments are to be completed within 4 weeks prior to the first study medication administration, unless specified otherwise.
3. To be completed prior to any other screening procedure.
4. To be completed within 6 weeks prior to the first study medication administration.
5. To be completed at 6 weeks prior to the first study medication administration.
6. To be performed if a muscle cell or fibroblast culture is not previously established and analyzed at RNA level for presence of DMD gene exon mutation(s) correctable by exon 51 skipping

7. Vital signs include blood pressure, pulse and respiratory rate
8. Cohort 1 only
9. Cohort 1, 2, 3 and 4t
10. Cohort 2, 3 and 4
11. Only if withdrawal is before the two muscle biopsies have been collected
12. Timed tests consist of: 10-meter walk/run, rising from floor, stair climb
13. See Table 5 for the time points

Table 5. Schedule of assessments during each hospitalization (visit 2-6) in study period

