| Concomitant medication          | x-----x           |     |                |                |                |                |                |                |                |                  | x                                     |

1. Baseline assessments will be done at time point 3 to 0 hours prior to dosing
2. The investigator will contact the subject/parent two days after release from the institute to enquiry about the health of the subject and to assess the adverse events and concomitant medication.
3. Vital signs include blood pressure, pulse and respiratory rate
4. At visit 2 (day 1) and visit 6 (day 29) only
5. At visit 2 (day 1) only
6. At visit 2 (day 1), visit 3 (day 8) and visit 5 (day 22) only
7. Optional
8. Timed tests consist of: 10-meter walk/run, rising from floor, stair climb
9. At visit 3 (day 8), visit 4 (day 16) and visit 5 (day 22) only

Table 6. Schedule of assessments for visits 13 – 37 (treatment beyond study period)

| Visit                                        | 13         | 14  | 15   | 16   | 17             | 18   | 19   | 20   | 21             | 22   | 23   | 24   | 25             | 26   | 27   | 28    | 29             | 30    | 31    | 32    | 33             | 34    | 35    | 36    | 37             | Withdrawal
prior to visit
37 |
|----------------------------------------------|------------------------|-----|------|------|----------------|------|------|------|----------------|------|------|------|----------------|------|------|-------|----------------|-------|-------|-------|----------------|-------|-------|-------|----------------|------------------------------------|
| Day (window ± 1 day)                         | d          | d+7 | d+14 | d+21 | d+28           | d+35 | d+42 | d+49 | d+56           | d+63 | d+70 | d+77 | d+84           | d+91 | d+98 | d+105 | d+112          | d+119 | d+126 | d+133 | d+140          | d+147 | d+154 | d+161 | d+168          |                                    |
| Week                                         | w          | w+1 | w+2  | w+3  | w+4            | w+5  | w+6  | w+7  | w+8            | w+9  | w+10 | w+11 | w+12           | w+13 | w+14 | w+15  | w+16           | w+17  | w+18  | w+19  | w+20           | w+21  | w+22  | w+23  | w+24           |                                    |

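### The escalation review is said to cover three doses at visit 4, but visit 4 blood and urine are taken before the third dose, so the required liver, kidney and platelet results cover only two

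*Protocol*

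**What the plan says.** The synopsis (Design and methodology) states that before each escalation "the safety data of the first three weekly administrations of PRO051 will be reviewed". Section 3.1 sets the minimum for each patient as data "up to and including the first three administrations of study medication (i.e. at least up to and including visit 4". It thus treats visit 4 as meeting the three-dose requirement.

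Section 3.3.1 places dosing on days 1, 8, 15, 22 and 29 (visits 2 to 6), so visit 4 is the day of dose three. Appendix 2, Table 5 is headed "Schedule of assessments during each hospitalization (visit 2-6) in study period" and therefore governs visit 4. It marks safety biochemistry, safety hematology and urinalysis in the t=-3 column only. Its footnote 1 defines that column: "Baseline assessments will be done at time point 3 to 0 hours prior to dosing". The rows for aPTT, complement and cytokines, and the dosing-day ECG, carry footnote 4: "At visit 2 (day 1) and visit 6 (day 29) only".

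Two other provisions affect timing. At 96 hours after dosing, "patients will be contacted by telephone by the investigator to enquire about adverse events and concomitant medication" (section 3.3.1). Section 3.2.4 says that "there will be an interval of at least 2 days between the start of treatment of each patient within one group".

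**The concern.** The rule equates visit 4 with three doses. That holds for what is observed after the injection: adverse events, vital signs, physical examination and local tolerability. It does not hold for the routine laboratory data, which at visit 4 come from before the injection. aPTT, complement and cytokines do not fill the gap, because after dose one they are next taken at visit 6.

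The rule controls steps from 0.5 to 2 to 6 to 10 mg/kg in boys aged 5 to 16. Some of the toxicity in section 1.3.2 would be expected clinically: past experience with the class indicates that "fever and chills may be dose limiting toxicities". Other effects would be found by laboratory test. At high doses, mice and rats showed signs of liver toxicity, and rats also some impairment of kidney function. Section 5.6.5.1, written for the extension, treats liver, kidney and platelet monitoring as critical. A reader of the synopsis or section 3.1 would assume that each escalation rested on three doses of such data, when the rule guarantees two.

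**Working it through.** **1. Doses behind each routine laboratory sample.** The protocol's own figure is three administrations at visit 4. Inputs are the visit days (section 3.3.1), the visits with routine blood and urine (sections 5.3.4.1 and 5.3.4.3) and the pre-dose timing (Table 5).

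| Visit | Day | Doses given before the sample |
|---|---|---|
| 2 | 1 | 0 |
| 3 | 8 | 1 |
| 4 | 15 | 2 |
| 5 | 22 | 3 |

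The stated three is not reproduced for laboratory data: visit 4 gives two, and three is first reached at visit 5.

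**2. How many boys can lack a result after dose three.** Let starts be *s* days apart, with *s* at least 2, and ignore laboratory reporting time. On the group calendar the third boy's 24-hour point after dose three is day 16+2*s* and his 96-hour call is day 19+2*s*. The three visit 5 samples fall on days 22, 22+*s* and 22+2*s*.

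| *s* | Call awaited? | Earliest cut-off | Visit 5 days | Boys lacking visit 5 |
|---|---|---|---|---|
| 2 | no | 20 | 22, 24, 26 | 3 |
| 3 | no | 22 | 22, 25, 28 | 2 |
| 5 | no | 26 | 22, 27, 32 | 2 |
| 6 | no | 28 | 22, 28, 34 | 1 |
| 2 | yes | 23 | 22, 24, 26 | 2 |
| 3 | yes | 25 | 22, 25, 28 | 1 |
| 7 | yes | 33 | 22, 29, 36 | 1 |

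The last boy always lacks it, since his own day 22 comes after his day 16 and his day 19.

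**3. Exposure at the time of the sample.** Section 1.3.2 gives half-lives of 1 week (kidney), 4 weeks (liver) and 27 days (terminal, plasma) from animal work. After *n* weekly doses the pre-dose level as a fraction of steady state is 1 − 2^(−7*n*/half-life).

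| Half-life | Visit 4 (*n*=2) | Visit 5 (*n*=3) |
|---|---|---|
| 7 days | 0.750 | 0.875 |
| 27 days | 0.302 | 0.417 |
| 28 days | 0.293 | 0.405 |

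**4. Illustration of the effect on the rule.** The protocol gives no rate of dose-limiting toxicity (DLT), so these inputs are assumptions: a five-dose DLT rate *p* of 20, 30 or 40% per boy, equal risk per dose, and a share *f* of DLTs visible only by laboratory test. A boy with full data contributes three of five doses, and a boy without the visit 5 sample loses the share *f* of one dose. With *m* such boys, the probability that a group of three shows no DLT is (1 − *p*)^(9/5 − *f·m*/5).

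| Case | *p*=0.2 | *p*=0.3 | *p*=0.4 |
|---|---|---|---|
| Visit 5 required, or *f*=0 | 0.669 | 0.526 | 0.399 |
| *f*=0.5, *m*=1 | 0.684 | 0.545 | 0.420 |
| *f*=0.5, *m*=2 | 0.700 | 0.565 | 0.442 |
| *f*=0.5, *m*=3 | 0.716 | 0.586 | 0.465 |
| *f*=1, *m*=3 | 0.765 | 0.652 | 0.542 |

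The largest gap is 0.542 − 0.399 = 0.143. If the call is awaited (*m* is 1 or 2) and *f*=0.5, the gap runs from 0.684 − 0.669 = 0.015 to 0.442 − 0.399 = 0.043.

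**The case against.** The strongest reply is that section 3.1 sets a floor and names it openly. It nowhere promises a blood sample after dose three, safety data of a clinical kind do exist after that dose, and any visit 5 result already in hand must be reviewed. All of this is true. But permission to wait is not a requirement, and presenting visit 4 as equivalent to three administrations is incorrect for the laboratory data.

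Other safeguards exist. The investigators and the sponsor's medical representative review each step and may lower the next dose (section 3.2.1). A medical monitor and an external committee follow safety (section 8.3). The earlier group is still sampled at visits 5, 6, 7, 9 and 12, so a late signal would surface, though possibly after the next group has started dosing. These measures limit the harm but do not supply the missing result at the decision.

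The toxicity background is also milder than it may sound. Monkeys, which section 1.3.2 considers more predictive, showed kidney tubular granules but neither tubular degeneration nor a fall in platelets up to 140 mg/kg/wk. Rodent liver toxicity appeared from 175 mg/kg/wk in mice and 56 mg/kg/wk in rats, which is 17.5 and 5.6 times the top dose of 10 mg/kg. The emphasis in section 5.6.5.1 concerns long-term dosing. This limits how serious the gap is.

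Finally, the DLT rates and laboratory-only share are assumptions, the equal-risk model ignores accumulation, and even visit 5 sees only about 41% of steady-state liver exposure. These points stand, but the schedule count needs none of those assumptions.

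**Conclusion.** The concern holds. At the minimum cut-off, routine liver, kidney and platelet results cover two of the three doses, while aPTT, complement, cytokines and dosing-day ECG cover dose one only. One to three of three boys can lack a laboratory result after dose three, and the last-enrolled boy always does. This follows from the visit schedule alone.

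The practical effect is less certain. Under the assumed rates, the chance of a group showing no DLT is overstated by 0 to 14 percentage points. Zero applies if all DLTs are clinical. The top figure needs all DLTs to be laboratory-only, a 40% rate, starts 2 days apart and no wait for the call. If the call is awaited and half of DLTs are laboratory-only, the range is 1.5 to 4.3 points. The change should be made because it is cheap and concerns an escalation rule in children, but the gap does not invalidate the design.

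**What to change.** In section 3.1 and the synopsis, set the minimum cut-off to include each boy's visit 5 (day 22) pre-dose biochemistry, hematology and urinalysis. State there that aPTT, complement, cytokine and dosing-day ECG data at the review come from dose one. No extra peak-time sampling is needed, since section 1.3.2 reports that peak levels and the related acute effects did not appear to grow with repeated dosing.

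Section 8.3 speaks of the core part as completed, so rewording cannot alter escalations already made. The core study report should therefore state, for each escalation, which doses the laboratory data covered.

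Had it applied from the outset, the cost per escalation would be at most 22 − 15 = 7 days from the third dose, or 22 − 16 = 6 days beyond the 24-hour point and 22 − 19 = 3 days beyond the 96-hour call. Over three planned steps that is at most 3 × 7 = 21 days. There is no added visit, sample or blood volume. Dose levels, group sizes and the decision model in Table 2 are unchanged.
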